## 6.3 Questioning rest after SRC

Observational studies have consistently documented the negative consequences of inactivity in various conditions^18^. Sedentary behavior following injury/illness is the most consistent risk factor for chronic disability^58^, and prescribed rest may begin to adversely affect the cardiopulmonary and musculoskeletal systems in healthy people within just three days^59^. Inactivity may also exacerbate and/or prolong recovery in commonly identified mTBI comorbidies such as vestibular disorders, mental health disorders, chronic fatigue syndrome, and pain disorders^18^. Athletes in particular are vulnerable to the deleterious effects of prolonged rest with respect to physical deconditioning, as well as secondary symptoms arising from fatigue and reactive depression^31^.

## 6.4 Utility of Exercise in CNS Injuries

The positive effects of structured AE on recovery exists for a number of CNS injuries^18^. Exercise has been shown to influence multiple neurotransmitter systems and promote neuroplasticity, neurogenesis, and angiogenesis following a traumatic event^20,22^. Specifically, limiting bed rest and initiating AE has been associated with positive outcome for stroke^60,61^, whiplash^62,63^, and low-back pain^64,65^ patients.

The evidence supporting AE intervention after TBI is promising, but predominantly limited to animal experimentation. The initiation of exercise training shortly after TBI in rats may be an important facilitator of recovery from cerebral dysfunction, due to neurogenesis and the proliferation of neuronal stem cells surrounding the injured site^29,66^. In addition, voluntary AE initiated immediately following injury has been shown to significantly inhibit apoptosis of neurons and decrease hippocampal DNA fragmentation in injured areas of the brain, leading to improvements in cognitive function and memory^35,67^. Lastly, AE following TBI has also been associated with enhanced survival of Purkinje fibres and the suppression of reactive astrocyte formation^36^.

## 6.5 Utility of exercise after concussion

AE has benefited adults and children who are slow to recover after concussion^40,68^. The scientific basis for recommending AE in the treatment of concussion includes its ability to improve cortical connectivity and activation^69^, facilitate neurogenesis, and regulate cerebral blood flow (CBF) and reactivity.

Exercise is associated with greater levels of brain-derived neurotrophic factor (BDNF), which is involved in neuron repair, increasing hippocampal volume, and improving spatial memory^70^. Moreover, as prolonged rest after TBI may lead to physical deconditioning of the cardiovascular system and a resultant impairment of CBF control, exercise training and physical fitness can improve CBF control and cerebral vasoreactivity^71^.

Functional magnetic resonance imaging (fMRI) studies show an excess of metabolic activity during simple cognitive tasks post-injury^72,73^, suggesting decreased efficiency in the concussed brain. AE treatment has been shown to restore fMRI brain activation patterns to normal compared to a sham (stretching) program, and is associated with persistent symptom resolution, including fatigue^40^. Similarly, Gagnon and colleagues found that the implementation of an active rehabilitation intervention was associated with significantly decreased post-concussion symptoms, as well as decreased fatigue and improved mood in a group of adolescents who were still symptomatic at four weeks post-SRC.^74^

Despite the promise of the benefit of exercise in those with persistent symptoms, there is a void of prospective studies investigating the efficacy of graded AE rehabilitation strategies in concussion patients at the sub-acute phase of recovery. In view of this, a retrospective study by Majerske and colleagues found that athletes engaging in a medium level of physical and cognitive activity post-injury had fewer symptoms and performed better on neurocognitive testing compared to those with no activity and the highest levels of activity^37^. These findings further support the potential benefit of exercise post-concussion, and warrant future prospective investigations.

## 6.6 Knowledge Gaps

As adolescents and young adults represent the overwhelming majority of concussion patients^75,76^, the development of a safe, effective, and evidence-based rehabilitation strategy is imperative for this population. Yet, despite emerging evidence demonstrating the efficacy of exercise interventions in the treatment of various CNS injuries (i.e. stroke, whiplash, low back pain, dementia), very few studies have examined the clinical utility of alternative rehabilitation strategies beyond rest. While AE interventions have been evaluated in patients with prolonged symptomology, investigations on the effect of structured exercise early post-concussion have been limited to animal models of injury, or assessed in humans using a retrospective study design. Furthermore, these studies rely mainly on subjective reports of concussion-associated symptoms to indicate impairment, and generally do not involve objective biological markers of underlying pathological processes.

# 7.0 POTENTIAL BENEFITS AND RISKS

Physical Risks During the study, participants in the Structured Aerobic Exercise Protocol (SAEP) group may experience an increase in their symptoms due to physical exertion. Should symptoms increase during a session, the session will be terminated immediately. If a participant in the exercise group experiences an increase in their symptoms over the course of two consecutive sessions, then their participation in the SAEP intervention will be terminated. While these participants will be removed from the larger group analysis, careful evaluation of this potential subset will be conducted. In addition, these participants will remain in the study and they will complete assessments on Days 7, 14, 21, 28, and 90 post-injury. In order to ensure the safety of all participants, there will be an on-call physician at all times available at the David L. Macintosh Sports Medicine Clinic, which is located directly next to the lab space in which the exercise sessions will take place.

Participants in the SAEP may also experience symptom exacerbation later in the day following the exercise intervention, even after they have left the testing facility. In order to minimize this risk, participants will be kept at the facility for an additional 10 minutes following the completion of the entire exercise session (including the 5 minute cool-down period) in order for the supervising researcher to monitor their symptoms and ensure that they their HR and BP have returned to pre-exercise levels. Additionally, participants in this group will be provided with the contact information for the David L. Macintosh Clinic, where a sports-medicine physician will be available on-call at all times should the participant require urgent care after they have left the facility. Finally, there may be minor and temporary discomfort associated with the blood-drawing procedure. This may include soreness or bruising of the skin in area of the blood-draw. This should resolve within a few days after the blood draw. Risks of experiencing infection or irritation of the skin surrounding the site of the blood acquisition will be minimal due to the training of the phlebotomist on site. If a sample cannot be acquired due to difficulties in locating a vein, or if a vein collapses, we will ask the participant if they are comfortable with one additional attempt on the opposite arm. If they are not comfortable with this, or if we are unable to acquire a sample on the other arm, we will terminate the blood acquisition portion of the assessment for the participant. Psychological/Emotional Risks Participants may become upset or frustrated if they lack progress in their perceived recovery time. In order to mitigate the potential mental health-associated risks that may arise due to participation in this study, participants’ will be given priority scheduling to be seen by a physician at the Macintosh Clinic, who will monitor them for mental health-related symptoms and refer them for psychiatric care if necessary. In addition to including the contact information for the Macintosh Clinic, the informed consent documents have been updated to provide participants with the contact information for local mental health treatment centres in the area that they may access should they require additional psychiatric resources.

Participants in both groups (Usual Care, and SAEP) will benefit from their participation in this study with respect to enhanced education on concussion and the various assessment measures associated with it (i.e. HRV, BPV, symptoms, and peripheral serum sampling). Participants will also benefit from this study as it will give them the opportunity to be seen by a sport-medicine physician every week for four weeks, which is far more medical attention than a normal concussion patient would receive. These patients would also be offered priority scheduling at the Macintosh Clinic. Furthermore, participants who follow the standardized exercise protocol who then may experience a faster recovery time than those managed with the current RTP management protocol, based on the evidence brought forth by previous literature in the field of neurorehabilitation and exercise. Moreover, participants in the exercise group will be given access to exercise equipment and supervision they would not otherwise be able to make use of. We anticipate that this study will facilitate significant progress to the sports medicine community. As a result of this study, our research team will be able to empirically compare both novel and current RTP management protocols. Given the lack of clinically validated rehabilitation strategies that currently exist in the management of SRC, this study has the potential to provide evidence of the clinical utility of a standardized, structured AE rehabilitation program for patients in the post-acute phase of recovery from SRC.

# 8.0 OBJECTIVES

**Specific Aim 1:** To investigate the utility of an Structured Aerobic Exercise Protocol (SAEP) initiated in the sub-acute phase after SRC in reducing post-concussion symptoms and the time to medical clearance, compared to usual care.

***Hypothesis 1 – Clinical recovery:***

Individuals in the SAEP will have lower symptom scores and faster return to asymptomatic status, leading to shorter clinical recovery times compared to those in usual care group.

**Specific Aim 2:** To determine the effect of an SAEP in concussed subjects on ANS function, blood biomarkers, and cognition.

***Hypothesis 2a*** – Cardiovascular responses:

Compared to the SAEP, the usual of care group will display lower HRV and BPV at days 14, 21, and 28 post-SRC.

***Hypothesis 2b:*** *- Peripheral blood biomarkers:*

As compared to the usual of care group, the SAEP group will display higher peripheral concentrations of neuroreparative indices BDNF and PRDX-6, lower concentrations of the CNS-injury analogue GFAP, lower concentrations of the inflammatory marker MCP-1, and lower resting peripheral catecholamine levels.

***Hypothesis 2c –Cognition:***

Compared to the usual care group, the SAEP group will display significantly improved cognitive performance at days 14, 21, and 28 post-SRC.

# 9.0 STUDY DESIGN

**Design:** A single blinded, randomized, controlled trial with 7-, 14-, 21-, 28-, and 90-day follow-up visits.

**Setting:** David L. MacIntosh Sport Medicine Clinic at the University of Toronto.

**Main Outcome Measures**: *Primary outcome measures*: post-concussion symptom scores and days to medical clearance; *Secondary outcome measures:* a) cardiovascular responses [heart rate variability (HRV) and blood pressure variability (BPV)], b) cognitive performance, and c) neuroinjury/neuroreparative blood biomarkers (BDNF, glial fibrillary acidic protein [GFAP], peroxiredoxin [PRDX]-6, monocyte chemoattractant protein [MCP]-1), and catecholamines (norepinephrine [NE] and epinephrine [Epi]).

**Intervention**: Structured Aerobic Exercise Protocol or Usual Care.

## 9.1 Participants

Participants will be recruited from the David L. Macintosh Sport Medicine Clinic (University of Toronto). The Macintosh Clinic is an interdisciplinary sport medicine clinic with a Concussion Program. The clinic is known for their acute management of concussions and is the primary clinical site for University of Toronto students who sustain physical activity related injuries. The clinic also has a number of existing relationships with local district schoolboards and sports organizations. These organizations are not founded on research participation, and do not require physician referral for concussion. The most recent estimate of new concussion cases in the clinic per year is approximately 300-350. Based on our previous research conducted at the MacIntosh Clinic^1,2^, as well as recent Canadian emergency department statistics^14^, we expect female participants to account for 40% of our study sample. Potential study participants will be examined and diagnosed with SRC within 72 hours of injury by one of the 3 physicians working at the clinic who specialize in concussion management. If the patient is diagnosed with a concussion, informed consent and study enrolment will occur after the first office visit. At Day 3 post-concussion, study eligibility will be confirmed by a Post-Concussion Symptom Scale (PCSS) evaluation used to determine their symptom status. The decision to wait three days post-injury to randomize participants and initiate the intervention is aligned with an approach based on the suggestion that rest beyond three days following mTBI is provides no further benefit to recovery^16^. At that time, symptomatic patients (defined as having a PCSS score equal to or greater than five on the SCAT5) will be randomly divided into one of two groups by a computer generator; this task will be overseen by a member of the research team not involved in the consent process. Our operational definition of “symptomatic” status (PCSS score 5 or greater) is based on prior literature, including a systematic review by Alla and colleagues, which suggests low PCSS scores are representative of the general population’s symptom presentation in a non-concussed state^77^**.**

## 9.2 Intervention

**(1) Usual care (UCEP) group:** Participants allocated to the UCEP group were advised to follow the instructions, prescriptions, and recommendations given to them by the sport medicine physician. Aligned with consensus guidelines of a brief period of physical and cognitive rest, the physician advised participants to increase their activity levels gradually with minimal head movement (predominantly involving a stationary bike) and progressively increase levels of exertion while remaining under the threshold of symptom exacerbation.^78^ Subsequently, exercise included a progression of head movements, visual and cognitive burdens, sport-specific activities, and heavy resistance, in that order, all below the symptom exacerbation threshold. For more details on the UCEP, please see the **Appendix**. Any diagnosed concomitant neck injuries underwent concurrent rehabilitation. Completion of asymptomatic low-risk simulations of target activities was required prior to medical clearance to return to those activities.

**(2) Structured Aerobic Exercise Protocol (SAEP) group:** These individuals will begin to exercise at Day 3 post-injury. Participants will be asked to complete a total of eight exercise sessions over the course of 11 days, with one day of rest after two consecutive sessions. The participants will have their symptoms recorded before and after exercise, and monitored throughout each session. Symptoms will only be recorded during exercise if exacerbated, in which case the session will be terminated. If this occurs, patient will resume the same stage in the protocol at the subsequent session. If the patient’s symptoms become exacerbated for two consecutive sessions, they will be removed from the study and continue with clinic for patient follow-up. Should the participant achieve asymptomatic status at any point, they will continue with the exercise protocol until completion, while simultaneously being guided through the RTP guidelines.

## 9.3 Inclusion

(1) Concussion diagnosis will be based on the following criteria: a) observed or reported acceleration/deceleration of the head; b) any observed alteration in mental status; and/or c) observed signs such as confusion, vacant stare, poor coordination, difficulty concentrating, poor balance; and/or d) any self-reported symptoms such as headache, loss of consciousness, nausea, balance problems or difficulty reading or concentrating; (2) Minimum grade 9 educational level; (3) Able to speak and understand English.

## 9.4 Exclusion

(1) Previous concussion within two weeks of the presenting SRC; (2) Presence of any co-morbid injuries (i.e. musculoskeletal/soft-tissue injuries, vestibular disorders); (3) Pre-existing heart condition or any uncontrolled seizure disorders; (4) History of medical or neurological conditions that affect cognitive functioning.

## 9.5 Structured Aerobic Exercise Protocol (SAEP)

The proposed exercise protocol will consist of 8 sessions, proceeding in a stepwise fashion with respect to duration and intensity over the course of 11 days, with two consecutive sessions proceeded by one day of rest. A fixed wattage stationary bike (Velotron Dyndafit Pro, manufactured by Racermate Inc., Seattle, WA, USA) will be used for all exercise sessions. The use of a stationary bike will ensure head and neck stability, avoiding any unwanted accelerations of the head (cf. treadmill). Finally, the bike will be connected to an interactive heart rate monitor (Polar®, Kempele, Finland), allowing the research team to control the wattage of the bike for each individual subject.

The first session of the AE protocol will take place on the Day 3 post-injury, and will comprise 15 minutes of steady-state exercise at 60% of the participant’s age-predicted maximal HR (apHR), plus a warm-up and cool-down period (25 minutes total). The participant’s symptoms will be monitored before, during, and after exercise. If the participant’s symptoms are not exacerbated, they will proceed to the next exercise level, consisting of 20 minutes of steady-state exercise, at 60% of apHR, plus warm-up and cool-down (30 minutes total). Please see **Table 1.** below for a detailed summary of the exercise protocol. Participants’ HR and BP will be recorded before and after each exercise session. Symptoms will also be recorded before and after each exercise session using the PCSS, and a trained kinesiologist will monitor symptoms throughout the exercise session. A prepared script to monitor symptoms has been developed to ensure standardization. If participants in the exercise group achieve asymptomatic status at the two weeks post-injury, they will continue to progress through the AE intervention until they complete all eight sessions, and will also begin progressing through the existing clinical RTP guidelines.

In an effort to improve our ability to evaluate the efficacy of the intervention, all participants will be given an activity tracker. The benefit of providing an activity tracker is the ability to monitor and quantify activities with daily living (ADL) beyond the study protocol (Supervised Exercise Group or Usual Care Group). Participants will be provided activity tracker (Fitbit Alta HR) at the time of consent to participate in the study and returned to the researcher at Day 28 assessment. Data to be collected by Fitbit Alta HR include steps (daily) and heart rate (daily per beats per min); this data will be used as potential co-variates when evaluating the efficacy of the intervention.

**Table 1.** AE exercise protocol

|  |  |  | **AE Protocol** | | | | | | | | |
| --- | --- | --- | --- | --- | --- | --- | --- | --- | --- | --- | --- |
| Day | 3 | 4 | 5 | 6 | 7 | 8 | 9 | 10 | 11 | 12 | 13 |
| Session | 1 | 2 | Rest | 3 | 4 | Rest | 5 | 6 | Rest | 7 | 8 |
| Duration (min) | 15 | 20 |  | 20 | 20 |  | 20 | 20 |  | 20 | 20 |
| Intensity (% apHR) | 60 | 60 |  | 65 | 65 |  | 70 | 70 |  | 75 | 75 |

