# 2.0 PROTOCOL SUMMARY

Title: Post-acute Structured Exercise Following Sport Concussion: a Randomized Controlled Study

Overview: This study will investigate the effect of structured, structured aerobic exercise protocol (SAEP) compared to usual care on clinical recovery from sport-related concussion (SRC) within the post-acute phase of injury. Participants will be randomized into one of two groups: (1) Supervised Exercise Group: participants will complete a total of eight exercise sessions over the course of 11 days, starting at Day 3 post-injury (two sessions (first and mid-point) will be done in the lab, and the remained will be home-based sessions); (2) Usual Care Group: individuals will undergo a period of physical rest and standard care. For the purposes of this study, "rest" will be defined as the avoidance of any activities beyond those of daily living, including participation in sport and physical activity.

Objectives: *Primary:* To investigate the utility of an SAEP initiated in the sub-acute phase after SRC in reducing post-concussion symptoms and the time to medical clearance, compared to usual care. *Secondary:* To determine the effect of an SAEP in concussed subjects on ANS function, blood biomarkers, and cognition

Outcome Measures: *Primary*: post-concussion symptom scores and days to medical clearance; *Secondary:* a) cardiovascular responses [heart rate variability (HRV) and blood pressure variability (BPV)], b) cognitive performance, and c) neuroinjury/neuroreparative blood biomarkers (BDNF, glial fibrillary acidic protein [GFAP], peroxiredoxin [PRDX]-6, monocyte chemoattractant protein [MCP]-1), and catecholamines (norepinephrine [NE] and epinephrine [Epi]).

Endpoints: *Primary:* Days to asymptomatic status and days to medical clearance *Secondary:* Cardiovascular, cognitive, and neuroinjury markers at Day 90 post-injury.

Population:

Age: 13-25 years, Sex: All

Inclusion Criteria:

Diagnosed with SRC by a physician at the David L. MacIntosh Sport Medicine Clinic

Able to speak and understand English

Exclusion Criteria:

Have had a previous concussion within two weeks of the presenting SRC

Have any co-morbid injuries (i.e. musculoskeletal/soft-tissue injuries, vestibular disorders)

Have a pre-existing heart condition

Have any uncontrolled seizure disorders or a history of medical or neurological conditions that affects cognitive functioning

Number of Sites: 1

Study Duration: 36 months

Participant Duration: 90 days

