## 14.2 Analysis of Secondary Endpoints

Furthermore, A mixed model ANOVA will be used to evaluate possible differences in symptoms, HRV, BPV, cognitive performance and blood biomarkers between the standard of care group and AE intervention group (between group analysis) across 6 time points; 7, 14, 21, 28, and 90 days post-SRC (within group analysis). If the data fails the required normality assumption, the appropriate transformation will be performed on all data. We expect approximately 40% females in our study sample, allowing for differential responses between males and females. We will perform separate Kaplan Meier analyses in males and females on time to medical clearance between the standard of care and AE intervention groups. Likewise, we will perform separate mixed model ANOVA analyses in males and females to evaluate differences between AE intervention and standard care groups for all aforementioned secondary measures.

Regarding blood biomarker analysis, each individual biomarker will only be included for statistical quantitation if they fall within the lower and upper limits of quantitation (LLOQ and ULOQ, respectively) as delineated by the manufacturer. All samples will be run in duplicate, and excluded if the coefficient of variance (CV) between duplicate samples is > 25%. Furthermore, mean statistical analysis will only be performed on biomarkers that have quantifiable samples in > 50%, in all groups in question. A quantifiable sample is 1) within the manufacturers quantitative range, and 2) displays a CV between duplicates of < 25%. In instances where one or both groups contain <50% quantifiable samples, differences between these groups will be evaluated by χ^2^.

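### PCSS is scheduled more often under SAEP than under usual care on Days 3–13, so days to asymptomatic status can be dated earlier under SAEP unless both arms are dated from the same assessments

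*Protocol*

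**What the plan says.** - **Endpoint.** Section 2.0 lists the primary endpoints as "Days to asymptomatic status and days to medical clearance".
- **SAEP arm.** Section 9.2: "Participants will be asked to complete a total of eight exercise sessions over the course of 11 days". Table 1 gives Days 3, 4, 6, 7, 9, 10, 12 and 13. Section 9.5: "Symptoms will also be recorded before and after each exercise session using the PCSS".
- **Both arms.** Section 9.0: "A single blinded, randomized, controlled trial with 7-, 14-, 21-, 28-, and 90-day follow-up visits". Section 14.2 analyses symptoms "across 6 time points; 7, 14, 21, 28, and 90 days post-SRC" (six are announced, five are listed). Section 7.0 offers participants in both groups "the opportunity to be seen by a sport-medicine physician every week for four weeks". Section 9.6.1 leaves further clinical follow-up to the treating physician.
- **Recognising recovery.** The SAEP paragraph of section 9.2 says: "Should the participant achieve asymptomatic status at any point, they will continue with the exercise protocol until completion". The parallel sentence in section 9.5 refers instead to asymptomatic status at two weeks after injury.
- **Cut.** The only PCSS cut stated is the eligibility rule in section 9.1: "symptomatic patients (defined as having a PCSS score equal to or greater than five on the SCAT5".

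No section says which PCSS record dates asymptomatic status, or that session scores are for safety only.

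**The concern.** A time-to-event endpoint that can only be observed when someone is assessed depends on how often that happens. Here the scheduled frequency differs by randomised arm from Day 3 to Day 13, while the exercise programme is being delivered. If every PCSS counts, the same true recovery day can be recorded sooner in the arm that is scored more often. An apparent benefit on one of the two primary endpoints could then come partly from surveillance. Any such shift favours SAEP, because the SAEP schedule contains every common visit plus the sessions.

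**Working it through.** The protocol gives no figure for this endpoint to reproduce, so the check applies the two schedules to the same true recovery day.

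**Inputs from the protocol**
- SAEP: Days 3, 4, 6, 7, 9, 10, 12, 13 (Table 1) plus 14, 21, 28, 90.
- Usual care: Days 7, 14, 21, 28, 90 (sections 9.0 and 14.2).
- 53 per arm, significance level 0.05 (section 13.0).

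**Step 1: dating by hand.** Recorded day = first scheduled PCSS on or after the true day T.

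| T | 4 | 5 | 6 | 7 | 8 | 9 | 10 | 11 | 12 | 13 | 14 |
|---|---|---|---|---|---|---|---|---|---|---|---|
| SAEP | 4 | 6 | 6 | 7 | 9 | 9 | 10 | 12 | 12 | 13 | 14 |
| Usual care | 7 | 7 | 7 | 7 | 14 | 14 | 14 | 14 | 14 | 14 | 14 |
| Later by | 3 | 1 | 1 | 0 | 5 | 5 | 4 | 2 | 2 | 1 | 0 |

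Mean for T = 4 to 13: (3+1+1+0+5+5+4+2+2+1)/10 = 24/10 = 2.4 days. From Day 14 the schedules coincide and the difference is 0.

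If usual care also had one discretionary score on Day 10, the differences become 3, 1, 1, 0, 1, 1, 0, 2, 2, 1, with mean 12/10 = 1.2 days.

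**Step 2: effect on a test when there is no treatment effect.** The protocol gives no distribution for symptom resolution. The 43-day mean in section 13.0 is for medical clearance. Assumption: T = 3 + (median − 3) × exp(0.6Z), with Z standard normal, the same in both arms, and the median varied. Each setting has 1,500 simulated trials and a two-sided 0.05 log-rank test on the recorded day. The share resolving by Day 13 is Φ(ln(10/(median − 3))/0.6).

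| Assumed median T (days) | 7 | 10 | 14 | 21 | 28 |
|---|---|---|---|---|---|
| Resolved by Day 13 | 94% | 72% | 44% | 16% | 6% |
| Mean shift, sessions v common visits (days) | 2.1 | 2.0 | 1.2 | 0.4 | 0.15 |
| Rejection | 99% | 80% | 23% | 5.5% | 4.5% |
| Mean shift, usual care also scored Day 10 (days) | 0.8 | 0.7 | 0.5 | 0.2 | 0.1 |
| Rejection | 64% | 22% | 8% | 5% | 5% |
| Rejection, both arms dated from common visits | 4.7% | 6.1% | 5.5% | 5.1% | 4.9% |

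In the first scenario the rejections at medians 7 to 14 are almost all in favour of SAEP. Simulation error at a true 5% is about ±1.96 × √(0.05 × 0.95/1500) = ±1.1 percentage points, so the last row is nominal.

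**Step 3: sensitivity to spread.** With 0.7 in place of 0.6, the test falsely favours SAEP in about 61%, 18–20% and 4–5% of trials at medians 10, 14 and 21, against a nominal 2.5% in that direction. The pattern is the same.

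**The case against.** The strongest reply is that nothing says session scores date the endpoint. Section 9.5 lists them beside heart rate and blood pressure, section 10.0 uses symptom monitoring to detect exacerbation, and section 14.2 analyses symptoms at the common days only. The statement in section 9.2 governs continuing exercise and starting return to play, not endpoint dating, and section 9.5 speaks of two weeks, which fits the Day 14 visit. A dating rule is often left to the statistical analysis plan, which is not shown. This stands in part: the bias is possible, not established. But the unequal collection is fixed by the protocol, nothing reserves session scores for safety, and a later plan cannot create usual-care scores that were never collected.

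Three stronger readings do not hold.

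- A reader might infer that usual care is scored only weekly. Section 9.6.1 permits extra evaluations in both arms, so this is true only of scheduled assessments.
- A reader might take the simulated rejection rates as the trial's false-positive rate. No log-rank or Cox analysis of this endpoint is specified: section 14.1 applies Cox regression to medical clearance only. The rates also rest on an assumed distribution. Section 5.0 cites recovery in 7–10 days but says that evidence is limited to collegiate and professional athletes, with longer times in younger patients.
- A reader might extend the point to days to medical clearance. That date comes from medical records under physicians meant to be blinded (sections 9.6.1 and 9.6.2), and this check does not show that it is affected.

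The check also assumes a PCSS at all eight sessions. Section 2.0 makes most of them home-based, and missed scores there would reduce the shift.

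**Conclusion.** The concern holds in conditional form. The scheduled PCSS differs by arm on Days 3–13, the dating record for a listed primary endpoint is not fixed, and first-qualifying-score dating would favour SAEP with no treatment effect: 0 to 5 days (mean 2.4) for true recovery on Days 4–13, and nothing from Day 14. How far this would distort a test depends on how many participants resolve before Day 14, which the protocol does not say, and on how often usual care is seen between visits. The inflation ranges from severe (median 7–10 days) to negligible (about 21 days or more). This is a worthwhile and inexpensive correction to the endpoint definition. It does not show that the trial's result will be biased.

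**What to change.** In sections 2.0 and 9.6, state that asymptomatic status is determined in both arms only from the PCSS at the common visits (Days 7, 14, 21, 28 and 90), using one stated cut. Section 9.6.3 should name the PCSS among the measures taken at those visits, which it does not now do. Analyse the endpoint as interval-censored between visits. State that session PCSS is for safety monitoring and does not enter the endpoint. Sections 9.2 and 9.5 differ on when asymptomatic status is recognised under SAEP and must be reconciled.

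The cost is a change of wording, an interval-censored analysis and coarser dating in the SAEP arm, by the 0 to 5 days shown above for early recoveries. Dating both arms from the common visits makes the shift zero by construction.

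If finer dating is wanted, an optional alternative is to collect the same PCSS remotely from usual-care participants on the SAEP session days. That keeps the resolution but adds data collection in that arm.
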